# Testing the feasibility of a knowledge translation intervention designed to improve chiropractic care for adults with neck pain disorders: study protocol for a pilot cluster-randomized controlled trial

**DOI:** 10.1186/s40814-016-0076-9

**Published:** 2016-07-20

**Keywords:** Neck pain, Knowledge translation, Chiropractors, Clinical practice guidelines, Multimodal care, Brief Action Planning, Feasibility outcomes, Cluster-randomized controlled trial

## Abstract

**Background:**

Neck pain in adults is common and a leading cause of physical disability. Recently, a guideline was developed for the management of non-specific neck pain (NSNP) with an aim to improve the quality of the delivery of chiropractic care. One key guideline recommendation is to undertake multimodal care for patients with NSNP. The aim of this pilot study is to determine the feasibility of implementing a multifaceted knowledge translation intervention by promoting the use of multimodal care by chiropractors managing patients with NSNP.

**Methods/design:**

The design is a cluster-randomized controlled pilot and feasibility trial. Chiropractors in private practice in Canada will be approached to participate in the study. Thirty consenting chiropractors will be randomized to receive either a theory-based educational intervention in the experimental group or simply a printed copy of the guideline in the control group. Each chiropractor will recruit five neck pain patients (a total of 150 patients) into the study. Development of the multifaceted intervention was informed by the results of a related qualitative study based on the Theoretical Domains Framework and consists of a series of three webinars, two online case scenarios, a self-management video on Brief Action Planning, and a printed copy of the practice guideline. *Primary feasibility outcomes* for both chiropractors and patients include rates of (1) recruitment, (2) retention, and (3) adherence to the intervention. A checklist of proxy measures embedded within patient encounter forms will be used to assess chiropractors’ compliance with guideline recommendations (e.g. exercise and self-care prescriptions) at study onset and at 3 months. Secondary outcomes include scores of behavioural constructs (level of knowledge and self-efficacy) for recommended multimodal care. *Clinical outcomes* include pain intensity and neck pain-specific disability. Analyses from this study will focus on generating point estimates and corresponding 95 % confidence intervals for parameters of a priori interest (recruitment, retention, adherence, pain intensity, Neck Disability Index).

**Discussion:**

Results of this study will inform the design of a larger cluster-randomized controlled trial aimed at evaluating the effectiveness of the theory-based tailored intervention and increasing the use of multimodal care by chiropractors managing patients with NSNP.

**Trial registration:**

https://clinicaltrials.gov/, NCT02483091

**Electronic supplementary material:**

The online version of this article (doi:10.1186/s40814-016-0076-9) contains supplementary material, which is available to authorized users.

## Background

Translating evidence into clinical practice is challenging. As a result, patients often fail to receive optimal care and may be exposed to unnecessary harm [1]. The Medical Research Council (MRC) guidelines on complex intervention evaluation recommends conducting feasibility and/or pilot studies with an aim to improve the effectiveness and efficiency of interventions and to address the challenges in translating research into real-world settings [2, 3]. One example where these recommendations apply is within clinical sites that deliver interventions for individuals with musculoskeletal (MSK) conditions.

Neck pain results in an enormous social, psychological, economic burden to society and is a leading cause of physical disability [4]. The estimated annual incidence of neck pain ranges between 10.4 and 21.3 % with a higher incidence noted in office and computer workers [5]. In chiropractic practice, neck pain accounts for approximately 25 % of initial consultations [6]. Opinions vary widely on what causes neck pain and how best to manage it [7]. The vast majority of patients with neck pain have symptoms that are “non-specific” in nature that cannot be attributed to a specific disease process or anatomical structure [8]. Perhaps as a result, relatively few treatments have been shown to achieve meaningful and sustained improvements in pain, physical function, and disability, despite associated high costs of neck pain [9].

Current evidence suggests a multimodal approach including manual therapy, providing self-management support to patients, and physical activity including exercise as an effective treatment strategy for acute and chronic neck pain [10]. The promotion of physical activity, including exercise, is a first-line treatment considered important in the prevention and treatment of musculoskeletal pain and its related co-morbidities [11]. For a minority of patients, clinician-delivered interventions and pharmacological treatments are appropriate, and in fewer cases, multidisciplinary pain management and/or surgery may be indicated [12]. In addition, multi- and/or inter-disciplinary multimodal therapy, as well as cross-sectorial integrated medical care appear to be cost-effective strategies for managing chronic pain [13].

Notwithstanding these recommendations, the contemporary management of non-specific neck pain (NSNP) is often suboptimal. For instance, a recent survey of Canadian chiropractors suggests that only 41 % of 2500 respondents provided advice to patients on self-management strategies. Another survey of chronic neck and back pain patients indicated that less than half of attending physicians, chiropractors, and physical therapists prescribed exercises [14]. Uninformative diagnostic testing, narcotics, and modalities tend to be over-utilized, while therapeutic exercise and activation tend to be under-utilized [13, 15]. For people with chronic NSNP, therapeutic exercise has a positive effect on pain and disability in the short (<1 month) and intermediate (1–6 months) terms [16]. However, when home exercises for neck or low back pain are prescribed, patient compliance is often poor with published adherence rates converging at about 50 % [17–19].

People with musculoskeletal pain will easily adopt an inactive lifestyle, possibly as a consequence of their physical impairment or because they believe that pain justifies physical inactivity [20]. Unfortunately, physical inactivity has major health effects worldwide. Physical inactivity is associated with many adverse health effects, including increased risks of coronary heart disease, type 2 diabetes, breast and colon cancers, and shorter life expectancy in general [21]. Ultimately, not only is increased compliance with prescribed condition-specific exercise likely to improve MSK-related complaints, but increased general physical activity may significantly reduce patients’ risks of developing serious co-morbidity.

A recent systematic review concluded that multifaceted knowledge translation (KT) interventions were no more effective than single-component KT interventions [22]. Nonetheless, there is growing evidence that active, multicomponent strategies are more effective in implementing change in professional behaviour [23–25]. Active, multicomponent strategies include the use of modalities such as interactive education [26] and printed educational materials (e.g. guidelines) [27]. In addition, a recent Cochrane review concluded that a tailored implementation intervention is more likely to improve professional practice than no intervention or dissemination of guidelines [28]. To date, very few studies have evaluated the impact of KT interventions in the chiropractic setting specifically [29].

### Context and purpose of the study

Recently, a clinical practice guideline (CPG) on the management of NSNP was updated with the aim of improving the quality of delivery of chiropractic care [30]. One of the key recommendations involves undertaking multimodal care for patients with acute and chronic NSNP. To facilitate the uptake of these recommendations, the Canadian Chiropractic Guideline Initiative (CCGI) (www.chiroguidelines.org) has developed and disseminated a multifaceted KT intervention (involving a combination of a webinar series, online clinical vignettes, and a learning module on self-care) [31]. Thus, the proposed overall aim of this study is to inform the design of a cluster-randomized controlled trial on the feasibility of implementing multimodal care in chiropractic practice.

### Research question and objectives

The research question of interest for a larger main study is the following: Among chiropractors in Canada, to what extent does the effectiveness of a multifaceted theory-based complex educational KT intervention plus provision of a copy of the CPG (for the intervention group) enhance behavioural change and compliance with a multimodal care programme when compared to the distribution of CPGs alone (for the control group) for the management of NSNP-related pain and disability over 3 months?

The immediate primary objective of the current pilot study is to provide evidence for the feasibility of conducting a fully powered cluster RCT to evaluate a complex KT intervention. Feasibility will be evaluated in terms of rates of recruitment, retention, and adherence to the study protocol. We will ascertain how closely participating chiropractors and patients adhere to the study protocol and will solicit feedback from them about the overall usefulness of the content and format of the KT intervention. The potential effectiveness of the complex KT intervention will also be estimated. Again, the results of this pilot trial will be used to design a full-scale cluster-randomized trial.

### Specific objectives

The specific objectives target two groups of participants: chiropractors and patients. For each group, both feasibility and efficacy potential will be estimated.For chiropractors, the feasibility objectives are to estimate the proportion who Are eligible to participate and are willing to be randomized; Comply to all study procedures, including completing the KT intervention component and implementing the CPG recommendations; and Complete the 3-month follow-up evaluation.
For patients, the feasibility objectives are to estimate the proportion who Are eligible to participate and are willing to be randomized; Adhere to all study procedures; and Complete the 3-month follow-up visit and all questionnaires.
For chiropractors, the efficacy potential objectives are to estimate The extent to which knowledge and self-efficacy changes after engaging in the KT intervention and CPG and The extent to which knowledge and self-efficacy changes after engaging in CPG.
For patients, the efficacy potential objective is To estimate the effect of their chiropractor’s KT intervention and CPG implementation changes in pain, disability, and satisfaction with care at the initial phase, as well as after 3 months of follow-up.
Other secondary objectives are to identify and provide solutions to Chiropractors’ concerns about the quality of the webinars; Potential impediments to successful initiation of the main study protocol after randomization; and Challenges that participating clinicians have with managing the study (e.g. with implementing the multimodal care and/or completing initial and follow-up questionnaires).

## Methods/design

### Design

This is a pilot cluster-randomized, two-arm, parallel-group controlled trial with a 1:1 allocation ratio. A cluster-randomized design has been chosen to avoid contamination between intervention and control arms by individual patients who would potentially be served by the same chiropractor in a non-cluster design. In addition, cluster-randomized trials offer logistical convenience when implementing certain interventions such as training, feedback, and supervision programmes, which are easier to administer to groups rather than individuals [32].

The study will test the feasibility and impact on protocol adherence and patient outcomes of two methods of delivering an educational intervention: (1) a KT complex intervention (theory-based KT intervention that includes three webinars, two case scenarios followed by a quiz, and Brief Action Planning) plus dissemination of practice guidelines for the intervention group and (2) passive dissemination of a practice guideline alone for the control group.

### Study setting and location

Our study setting and location are private practices of licensed chiropractors in Canada.

### Subjects/population

#### Recruitment of chiropractors

A sampling frame of 8200 chiropractic practices within 10 provinces in Canada will be obtained from the Canadian Chiropractic Association (CCA). From this, a random sample of 200 chiropractors will be selected and approached for participation in this study [33, 34]. A sample of 200 chiropractors has been chosen as we expect that 20 % of eligible chiropractors will agree to participate (i.e. recruitment rate), and from these, 80 % will complete the study at 3 months (retention rate). Chiropractors who agree to participate and meet the eligibility criteria will be randomized. If we are unable to recruit the required sample of 30 from the first wave of 200 chiropractors, an additional 200 chiropractors will be randomly sampled.

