### Measures

The key feasibility outcomes of interest include (1) study recruitment/participation, (2) adherence to the intervention, (3) study retention, and (4) KT intervention effectiveness potential. Table 1 provides the different criteria for defining the outcomes derived from items (1) to (4) above. Table 2 further summarizes the feasibility outcomes, sources of measurement, and timing of administration.

**Table 1 Tab1:** Criteria to assess feasibility

Construct	Parameter
	Eligibility proportion
Chiropractors	
Recruitment	Trial acceptance rate: >20 % agree to participate within 4 weeks
	Target population = 40 (assuming an 80 % retention rate)
Adherence to protocol	>90 % of participants will complete all 3 webinars, associated quizzes, 2 clinical vignettes, and a self-management learning module
Retention	80 % of participants will complete 3 months of patient follow-up
Patients	
Recruitment	Trial acceptance rate: 5 patients within 6 weeks of recruitment notice
	Target population = 150
Adherence to protocol	95 % will attend regular treatment sessions twice/week
	>80 % will comply with prescribed home exercise and physical activity
Retention	>80 % will complete patient encounter forms (VAS, NDI, and PSQ-18) and follow-up at 3 months

**Table 2 Tab2:** Outcome measures

Outcome	Source	Description of measures	Data collection time points	
Feasibility				
Recruitment	Chiropractors and patients	Measured as a proportion of chiropractors and patients potentially eligible for participating	Initial stage	
		Eligibility rate = number of eligible chiropractors and patients divided by the number of invited chiropractors or patients		
		Participation rate = number of chiropractors and patients agreeing to participate divided by number of eligible chiropractors and patients		
Adherence to protocol	Chiropractors	For those randomized to intervention arm, measured through the rates of attendance of all 3 webinars, associated quizzes, completion of 2 clinical vignettes, and the self-management learning module	Within 6 weeks of assignment	
	Patients	Rate of adherence to follow-up visits, prescribed home exercise, and physical activity	Baseline	3 months
Adherence perception (knowledge and self-efficacy)	Chiropractors and patients	Completion of questionnaires	Baseline	3 months

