### Trial status

At the time of writing, 45 chiropractors have agreed to participate in the study and have been randomized to the intervention and control groups. Participants have started recruiting neck pain patients. Results are expected in May 2016.

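### The number of chiropractors to randomize is 30 in the abstract and recruitment section but 40 in Table 1; by the plan's own rates 30 fits only as a number of completers

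*Protocol article*

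**What the plan says.** The abstract (Methods/design) states that "Thirty consenting chiropractors will be randomized to receive either" the educational intervention or the printed guideline. It gives each chiropractor five patients, for a total of 150.

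The section Recruitment of chiropractors says that "a random sample of 200 chiropractors will be selected and approached for participation in this study". Its agreement rate is worded as "we expect that 20 % of eligible chiropractors will agree to participate (i.e. recruitment rate"). Its retention rate at 3 months is 80 % of those who agree. It then draws a further 200 "If we are unable to recruit the required sample of 30 from the first wave of 200 chiropractors".

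Table 1 (Measures), in the chiropractor recruitment row, reads "Target population = 40 (assuming an"; the assumption named there is retention of 80 %. The same table sets the patient target at 150 and chiropractor retention at 80 %. Table 2 divides retention by the number randomized and participation by the number eligible.

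The section Recruitment of patients has each chiropractor enrol up to five patients. Trial status reports that "45 chiropractors have agreed to participate in the study and have been randomized".

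**The concern.** Recruitment, retention and adherence rates are the primary outcomes of this pilot, so the recruitment target is one of the benchmarks against which feasibility will be judged. With 30 in two places and 40 in a third, a count between 30 and 39 meets one statement of the target and misses the other.

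The difference also drives an operational rule. The second wave is tied to 30 recruits, which leaves no allowance for the 20 % loss that the same paragraph expects. The patient target of 150 is built on 30 as well, so it does not follow from Table 1's 40 unless one knows which chiropractors are being counted.

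**Working it through.** **Inputs.** Approached: 200. Agreement: 20 % of eligible. Retention: 80 % of those who agree (all three from Recruitment of chiropractors; 80 % again in Table 1). Patients per chiropractor: 5 (abstract; up to five in Recruitment of patients).

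**Reproducing the plan's figures.**
- Recruited = 200 × 0.20 = 40. This is Table 1's target.
- Completing = 40 × 0.80 = 32. This is enough for 30.
- Backward from 30 completers: 30 / 0.80 = 37.5, so 38 to randomize, close to 40.
- Patients = 30 × 5 = 150. This is the stated patient target.

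The figures 40, 30 and 150 therefore belong to one chain, provided that 30 means completers.

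**Taking 30 as written (recruited and randomized).**
- Completing = 30 × 0.80 = 24.
- Patients under completing chiropractors = 24 × 5 = 120 at most.

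**Taking 40 as randomized.**
- Patients at full quota = 40 × 5 = 200.
- Patients under completers = 32 × 5 = 160.
- If 150 is the total over all 40, each enrols 150 / 40 = 3.75 on average, below the five in Table 1.

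**The second-wave trigger.** It opens only below 30 recruits. At 30 to 39 recruits it stays shut although Table 1's 40 is missed. From 30 to 37 recruits the expected number of completers is also below 30 (37 × 0.80 = 29.6; 38 × 0.80 = 30.4).

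As an illustration, assume that all 200 are eligible and act independently:
- P(at least 30 recruits) = P(Bin(200, 0.20) ≥ 30) = 0.972.
- P(at least 30 completers) = P(Bin(200, 0.16) ≥ 30) = 0.679.
- Thirty completers require at least 30 recruits, so the chance that the trigger stays shut and yet fewer than 30 complete is 0.972 − 0.679 = 0.293.
- With exactly 40 randomized, P(at least 30 complete) = P(Bin(40, 0.80) ≥ 30) = 0.839.

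**Sensitivity to eligibility.** The 20 % applies to eligible chiropractors, but 40 results only if all 200 are eligible. The overall eligibility rate is not given.
- Removing only prior registrants (over 700 in a frame of 8200, about 8.5 %): 183 eligible, 36.6 recruited, 29.3 completing. This is still about 30 completers.
- Assumed range of 75 to 100 % eligible: 30 to 40 recruited and 24 to 32 completing.

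**The case against.** The strongest reply is that nothing is wrong with the numbers themselves. Retention is 80 % in both places, 200 × 0.20 × 0.80 = 32 covers 30, and 32 × 5 = 160 covers 150. On that view 30 is plainly a completer count, and the defect is one of wording. This largely stands, and it limits the point to labels and what hangs on them. It does not remove the point: no sentence calls 30 completers, three labels say otherwise, and the trigger acts on recruits.

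One could also note that 30 is the recruited number if 75 % of the 200 are eligible. The document states no such rate, and Table 1's 40 would then be out of reach from the first wave.

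Several stronger readings are tempting and are not supported:
- A reader might take 45 as a third target. It appears under Trial status as a count already achieved.
- A reader might infer that the plan's rates cannot deliver 30 chiropractors and 150 patients. They can, if 30 means completers.
- A reader might compute acceptance as 30/200 = 15 %, or 30/400 = 7.5 % over both waves, and set it against Table 1's bar of more than 20 %. Table 2 divides by those eligible, a number not given; with fewer than 150 eligible, 30 recruits would exceed 20 %. Nor does the text say that recruitment stops at 30.
- A reader might argue that 80 % chiropractor retention caps patient retention at 80 %, or that 0.80 × 0.80 = 64 % is the real expectation, against Table 1's requirement that more than 80 % "will complete patient encounter forms (VAS, NDI, and PSQ-18) and follow-up at 3 months". The cap needs chiropractors who drop out to enrol as many patients as the others and then lose every patient's 3-month data. The 64 % needs a separate within-practice rate. The document states neither; enrolment is up to five, and Table 2 also counts chiropractor completion through the chiropractor's own questionnaires.

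**Conclusion.** The inconsistency is real and narrow. The number of chiropractors to recruit and randomize is stated as 30 and as 40. The plan's rates make 40 the randomized number and 30 a completer number, so the abstract's wording and the second-wave trigger are wrong as written. Read literally, the gap is 24 completers against 32, and 120 patients under completing chiropractors against 160. The patient target of 150 does not say which chiropractors it counts.

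These sizes rest on 20 % agreement with all 200 eligible, 80 % retention and five patients per chiropractor. Lower eligibility lowers the yield but does not make 30 and 40 the same quantity.

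The severity is modest. The pilot has no power-based sample size, and the 45 already randomized exceed both figures. What remains at stake is which benchmark the results are reported against, and which number is carried into the main trial.

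**What to change.** State one chain and use it throughout: 200 approached, about 40 randomized, about 32 completing, with 30 as the minimum number of completers. Correct the abstract and Recruitment of chiropractors to match, and set the second-wave trigger at the randomized target of 40.

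State that the 150 patients are counted over about 30 completing chiropractors at five each, and say so in Table 1, where 150 now stands under recruitment. If 150 is meant over all randomized chiropractors, restate the figure; at five each it would be 200, which is added enrolment.

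Keep Table 2's all-randomized denominator for patient retention. Limiting it to patients of retained chiropractors would change a primary outcome and hide the loss of whole practices. Report the 45 as the achieved count beside the target of 40.

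The cost is restated figures. A trigger at 40 could have meant a further mailing, but with 45 already randomized it requires no new chiropractors now. Under the completer reading of 150, no additional patients are needed either.
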